**(3) Planned Participation Period per Subject**

**29 to 112 days**

- **Screening Period:** 1–56 days
- **Comparative Period:** 14, 21, or 28 days
  - The standard duration will be 21 days regardless of allocation.
  - If chemotherapy is administered in treatment cycles, the period will correspond to one cycle.
  - Minor adjustments due to outpatient schedules are permissible.
- **Continuous Period:** 14, 21, or 28 days
  - After completing the comparative period, participants continuing chemotherapy will receive both standard care (oral care, Episil® oral liquid, etc.) and the investigational device, irrespective of group assignment.

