|                           | concentration-dependent manner, thereby reducing biofilm formation on the cured surface.                                                                                                                                                                                                                                                                                                                                                                                                                                               |
| Mode of use        | Clean the tooth surface. Remove one single-use blister pack just before use. Using gloved fingers (preferably nitrile gloves that are easy to shape and non-sticky), directly apply the paste to the causative tooth. Remove excess material, ask the participant to occlude, adjust the shape, and initiate polymerization by light irradiation. If dislodgment is expected, bonding treatment should be applied before filling. Remove with an excavator or explorer if necessary. The device can remain in place for up to 30 days. |
| Properties         | / Light-curable paste composed of urethane dimethacrylate, polymer, silica, photoinitiator, and cetylpyridinium chloride.                                                                                                                                                                                                                                                                                                                                                                                                              |
| Specifications     |                                                                                                                                                                                                                                                                                                                                                                                                                                                                                                                                        |

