## ② Intervention Procedures

The comparative period (Day 1) begins on the day the investigational device is applied prior to chemotherapy. Chemotherapy should be initiated within three days after device placement (Day 0–3).

The evaluation timepoints are scheduled for Day 14, 21, or 28 of each treatment period, depending on the chemotherapy regimen.

After baseline assessments and interviews on Day 1 (before chemotherapy), interventions are conducted as follows:

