### 1) Comparative Period – Intervention Group

(Standard care [oral care, Episil® oral liquid, etc.] + investigational device)

- Record the start date of the comparative period.

- 226 • In addition to conventional oral care and protectants, the investigational device is applied to
- 227 teeth responsible for mucosal trauma (e.g., crowding, sharp edges due to fracture or attrition).
- 228 • If multiple candidate teeth exist, all will be filled and individually assessed.
- 229 • For procedural consistency, filling will be performed by the site investigator or co-
- 230 investigator (dentist).
- 231 • The light-curing and bonding process follows the method described above.
- 232 • The device remains in place throughout the 14–28-day period.
- 233 • If chemotherapy is postponed, the device will be removed and reapplied in coordination with
- 234 the rescheduled chemotherapy.
- 235 • After final evaluation (Day 14, 21, or 28), the device will be removed.
- 236 • If dislodged earlier, the date and time will be recorded.
- 237 • If continued application is deemed inappropriate or the participant wishes to discontinue, the
- 238 device will be removed and final assessments performed (see Section 14.5 Discontinuation
- 239 Criteria)

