## 240 **2) Comparative Period – Control Group**

241 (Standard care [oral care, Episil® oral liquid, etc.] only)

- 242 • Record the start date of the comparative period.
- 243 • Participants receive only standard care as per routine practice (see Section 6 for concomitant
- 244 treatments).
- 245 • After the comparative period evaluation, during the continuous period (Day 1–14/21/28), the
- 246 investigational device will be applied using the same procedure as the intervention group.
- 247 • Device removal, dislodgment recording, and discontinuation criteria are handled identically
- 248 to the intervention group.

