#### **(4) Confirmation of Adverse Events, Illnesses, and Device Malfunctions**

All adverse events, illnesses, and device malfunctions will be recorded in the electronic Case Report Form (eCRF), including details, onset/resolution dates, severity, treatment, outcome, seriousness assessment, and causal relationship to device use.

Follow-up investigations will be performed as needed.

Events occurring prior to device removal due to chemotherapy delay will also be included in safety evaluations.

Symptoms or disease progression attributable to the primary malignancy or to anticancer therapy itself will not be considered adverse events in this study.

For participants allocated to the control group during the comparative period, assessment of device-related malfunctions or causality is not applicable.

413 Schedule

| Period                                     | Screening period
a) / Enrollment     | Comparative period                   |                                              |                                    | Continuous period:
When chemotherapy is administered after the comparative period, existing therapy is combined with the filling of the investigational device irrespective of group assignment. |
|--------------------------------------------|-----------------------------------------|--------------------------------------|----------------------------------------------|------------------------------------|-----------------------------------------------------------------------------------------------------------------------------------------------------------------------------------------------------|
| Assessment date                            | —                                       | Day of study procedure
(Day 1) g) | End of comparative period (Day 14 / 21 / 28) | (At discontinuation)               | End of continuous period (Day 14 / 21 / 28)                                                                                                                                                         |
| Allowable range                            | Day -56 to Day -1
(before procedure) | Assessment date (Day 0)              | Assessment window: Day -7 to +7              | Discontinuation date (Day 0 to +1) | Assessment window: Day -7 to +7                                                                                                                                                                     |

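### For 28-day periods only, the -7 to +7 day evaluation window admits device removal up to Day 35, 4 to 5 days past the stated 30-day wear limit

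*Protocol*

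**What the plan says.** Under Mode of use in the device overview, Protocol section 4(4)①, the wear limit reads "The device can remain in place for up to 30 days". No other wear limit appears in the text available.

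Section 4(4)② fixes the day count: "The comparative period (Day 1) begins on the day the investigational device is applied prior to chemotherapy". For the intervention group it then ties removal to the evaluation: "After final evaluation (Day 14, 21, or 28), the device will be removed". Control participants receive the device in the continuous period, and the protocol states for them that "Device removal, dislodgment recording, and discontinuation criteria are handled identically" to the intervention group.

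The allowable-range row of the schedule table in section 5 gives "Assessment window: Day -7 to +7" for the end of the comparative period and again for the end of the continuous period. It makes no distinction between Day 14, Day 21 and Day 28.

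Section 4(3) permits periods of 14, 21 or 28 days and adds: "The standard duration will be 21 days regardless of allocation".

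**The concern.** Three rules meet here: a wear limit counted from application, a removal trigger counted from the evaluation, and one window for all three period lengths. If the window is wide enough, a visit can be on time for evaluation and too late for removal.

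A site that books 28-day visits from the schedule table alone could then exceed the only wear limit in the protocol without recording a visit deviation. Safety and dislodgement data from the extra days would describe use beyond that limit. The documents say nothing about what happens to the device or the patient after 30 days, so the stake is adherence to the stated conditions of use and the interpretation of those device data. It is not a demonstrated hazard.

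**Working it through.** **Inputs (all Protocol)**
- Wear limit: 30 days (section 4(4)①, Mode of use). This is a stated limit, so there is no derivation to reproduce.
- Application on Day 1; evaluations at Day 14, 21 or 28 (section 4(4)②).
- Evaluation window: -7 to +7 days, both periods (section 5, schedule table).
- Removal after the final evaluation (section 4(4)②, items 1 and 2).

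**Formulas**
- Latest on-schedule visit = nominal day + 7.
- Wear, elapsed count = visit day - 1. Wear, inclusive count (Day 1 counted as a day of wear) = visit day.
- Excess = wear - 30, or zero if negative.

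The protocol does not say which count the limit uses, so both are shown.

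**Latest on-schedule removal by period length**

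| Period | Latest visit | Wear, elapsed | Wear, inclusive | Excess |
|---|---|---|---|---|
| 14 days | 14 + 7 = Day 21 | 20 | 21 | 0 |
| 21 days | 21 + 7 = Day 28 | 27 | 28 | 0 |
| 28 days | 28 + 7 = Day 35 | 34 | 35 | 34 - 30 = 4 to 35 - 30 = 5 |

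**Where the excess begins in a 28-day period**

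| Visit day | Excess, elapsed | Excess, inclusive |
|---|---|---|
| 30 | 0 | 0 |
| 31 | 0 | 1 |
| 32 | 1 | 2 |
| 33 | 2 | 3 |
| 34 | 3 | 4 |
| 35 | 4 | 5 |

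The Day-28 window runs from Day 21 to Day 35, which is 35 - 21 + 1 = 15 days. Of these, Days 32 to 35 (4 days) lie past the limit on the elapsed count and Days 31 to 35 (5 days) on the inclusive count. Day 31 is exactly 30 elapsed days, so it exceeds the limit only on the inclusive count.

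**Check of the remedy**
- Upper bound +2: latest visit 28 + 2 = Day 30, wear 29 elapsed or 30 inclusive. Within the limit on both counts.
- Upper bound +3: latest visit Day 31, wear 30 elapsed or 31 inclusive. Within the limit on the elapsed count only.
- Window with +2: Day 21 to Day 30, which is 30 - 21 + 1 = 10 days.

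**The case against.** The strongest reply is that nothing is contradicted. A visit window says when an assessment may be made and does not authorise wear. Where a wider window meets a stricter device limit, the stricter rule governs, and a site that evaluates and removes by Day 30 satisfies every statement in the protocol. Planned wear is described as lasting 14 to 28 days. The discontinuation rule also lets the investigator remove the device and make the final assessments if continued application is judged inappropriate.

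Much of this stands. The 30-day limit does bind, and over-wear follows only if a site works from the window and overlooks the limit. But the schedule still classes as on time a visit that breaches the limit, and removal is attached to that visit. The discontinuation rule depends on judgement and is not a Day-30 rule.

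Two further replies limit the point. The available copy of the schedule table is incomplete, so a cap on removal in the missing part cannot be ruled out. And the reach is small and unknown: 21 days is standard, and the number of participants on 28-day periods is not stated and could be zero.

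A reader might also infer that late removal is built into 28-day cycles, since "Chemotherapy should be initiated within three days after device placement" and "If chemotherapy is administered in treatment cycles, the period will correspond to one cycle". With chemotherapy k days after application, the next cycle falls on Day 1 + k + 28 = Day 29 + k, so Day 31 or 32 for k = 2 or 3. The documents do not support that reading. It requires evaluation on the chemotherapy day itself, which the protocol does not specify. If the evaluation takes place when the next device is applied, again k days before chemotherapy, the visit falls on Day 29 + k - k = Day 29, within the limit on both counts. No frequency of late visits can be derived from the permitted lag.

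**Conclusion.** The concern holds as a minor misalignment confined to 28-day periods. The window admits on-schedule evaluation, and hence removal, up to Day 35: 34 elapsed or 35 inclusive days of wear, 4 to 5 days past the stated limit. Periods of 14 and 21 days comply throughout their windows.

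The conclusion rests on reading removal as following the actual evaluation visit, which is what the text says, and on there being no removal cap in the part of the schedule table that is not available. It does not show that any participant will exceed 30 days, that wear beyond 30 days is harmful, or that the efficacy comparison, sample size or power is affected.

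**What to change.** In the section 5 schedule table, set the Day-28 evaluation window to -7 to +2 days (Day 21 to Day 30) in both arms and both periods. Keep -7 to +7 for Day 14 and Day 21. Count device wear from the most recent application, because schedule footnote g) resets the application date when chemotherapy is postponed. For control participants in the comparative period, who wear no device, count from their recorded Day 1. Both arms are then graded in the same window, and evaluation and removal fall within 30 days on either count. An upper bound of +3 would be enough only if the limit is meant as elapsed days.

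Removing the device at Day 30 ahead of a later evaluation is not a good substitute. It would leave the target tooth uncovered before the primary grading, and in device wearers only.

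The change is one line in the schedule. The window for 28-day participants shrinks from 15 to 10 days, including for controls without a device. This may bring a few more visit deviations, or an occasional separate visit when the outpatient appointment would otherwise fall after Day 30.

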## ② Intervention Procedures

The comparative period (Day 1) begins on the day the investigational device is applied prior to chemotherapy. Chemotherapy should be initiated within three days after device placement (Day 0–3).

The evaluation timepoints are scheduled for Day 14, 21, or 28 of each treatment period, depending on the chemotherapy regimen.

After baseline assessments and interviews on Day 1 (before chemotherapy), interventions are conducted as follows:

### 1) Comparative Period – Intervention Group

(Standard care [oral care, Episil® oral liquid, etc.] + investigational device)

- Record the start date of the comparative period.

- 226 • In addition to conventional oral care and protectants, the investigational device is applied to
- 227 teeth responsible for mucosal trauma (e.g., crowding, sharp edges due to fracture or attrition).
- 228 • If multiple candidate teeth exist, all will be filled and individually assessed.
- 229 • For procedural consistency, filling will be performed by the site investigator or co-
- 230 investigator (dentist).
- 231 • The light-curing and bonding process follows the method described above.
- 232 • The device remains in place throughout the 14–28-day period.
- 233 • If chemotherapy is postponed, the device will be removed and reapplied in coordination with
- 234 the rescheduled chemotherapy.
- 235 • After final evaluation (Day 14, 21, or 28), the device will be removed.
- 236 • If dislodged earlier, the date and time will be recorded.
- 237 • If continued application is deemed inappropriate or the participant wishes to discontinue, the
- 238 device will be removed and final assessments performed (see Section 14.5 Discontinuation
- 239 Criteria)

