### **4. Method of Randomization**

Before the start of the study, the Randomization Supervisor will prepare a reproducible randomization table using computer-generated random numbers.

A stratified block randomization method will be applied, stratified by study site planned to conduct the comparative period.

The allocation ratio between the intervention and control groups will be **1:1**, based on the planned total sample size.

As this is an open-label study, detailed algorithmic parameters of the randomization will not be described in this protocol to prevent predictability of assignment and potential selection bias. Instead, they are specified in a separate *Randomization Specification Document*, which will remain confidential until all participants have been assigned.

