| Administration of G-CSF (yes/no)           | ●                                       | ●                                    | ●                                            | ●                                  | ●                                                                                                                                                                                                   |
| Blood tests (hematology and biochemistry)  | ● i)                         |                                      | ●                                            | ●                                  | ●                                                                                                                                                                                                   |

- c) Assessments marked accordingly must be performed prior to the investigational procedure.
- d) If the investigational device dislodges before the end of any treatment period, the date and time of dislodgement must be recorded in the patient diary.
- e) For participants assigned to the control group during the comparative period, the specified assessments and examinations for the comparative period are not required.
- f) Symptoms or disease progression related to the underlying breast cancer, as well as events directly caused by chemotherapy, are not regarded as adverse events in this study. Events occurring before device removal due to chemotherapy delay will still be evaluated. For participants in the control group during the comparative period, assessment of causal relationship between adverse events and device filling is not applicable.
- g) The day on which participants visit the site for device application prior to chemotherapy shall be defined as Day 1 (start of the comparative period). Chemotherapy should be administered within 0–3 days after device application, and the actual chemotherapy date must be recorded. If chemotherapy is postponed, the device should be temporarily removed, and the device application date reset in accordance with the rescheduled chemotherapy.
- h) Evaluate whether natural dislodgement, brushing-related dislodgement, meal-related dislodgement, or self-removal by the participant occurred. If such events occur before temporary device removal due to chemotherapy delay, they must also be included in the evaluation.

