### **Rationale:**

In the exploratory trial, the proportion of improvement in oral mucositis at Day 15 was 58.3% (7/12) in the intervention group and 0.0% (0/6) in the control group.

Considering the small control group size in the exploratory study, the uncertainty of the estimated effect, and the allowance of concomitant use of existing mucosal protectants (which may enhance control group outcomes), as well as inclusion of *prevention of onset* as an endpoint in this confirmatory study, the expected improvement rates were conservatively assumed as 50% in the intervention group and 25% in the control group.

With a two-sided significance level of 5% and 90% power using Pearson's chi-square test, 77 participants per group (total n=154) are required.

Based on previous accrual rates ( $\geq 10$  participants per year per site), this total sample size is feasible within the study period across the participating centers.

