#### **1. Full Analysis Set (FAS):**

All participants who were randomized, received treatment, and had at least one efficacy assessment (primary or secondary).

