### **(4) Protocol Amendments**

Safety-related information will be continuously reviewed, and the protocol and consent documents will be amended if necessary.

All amendments must be approved in advance by the Certified Review Board (CRB).

Amendments will be submitted to MHLW as follows:

739       • **Substantial amendment:**

- 740           1. *Notification of change in implementation plan* (Form No. 2, Ministerial Ordinance)  
741           2. *Revised implementation plan*

742       • **Minor amendment:**

- 743           1. *Notification of minor change in implementation plan* (Form No. 3)  
744           2. *Revised implementation plan*

745 For minor administrative changes (e.g., investigator contact details, institutional name updates),  
746 notification to the CRB will be made within 10 days, accompanied by submission of Form No. 3 to  
747 MHLW.  
748

749 **(5) Criteria for Discontinuation**

750 When continuation is deemed impossible, the investigator shall discontinue the participant's  
751 involvement, explain the reason if appropriate, and ensure that post-discontinuation medical care is  
752 provided without disadvantage.

753 **Reasons for discontinuation include:**

- 754       1. Participant requests to withdraw. (The reason will be confirmed if possible, but not required.)  
755       2. Worsening of primary disease, chemotherapy-related symptoms, or requirement for  
756       disallowed concomitant therapy.  
757       3. Occurrence of adverse events making continuation difficult.  
758       4. Noncompliance with the protocol.  
759       5. Ineligibility determined upon further observation after registration.  
760       6. Any other reason judged by the investigator to make continuation inappropriate.

761 **In case of treatment discontinuation:**

762 If continuation of the investigational treatment is deemed impossible for the above reasons, treatment  
763 will be discontinued with an appropriate explanation to the participant.

764 Participants who have received the investigational device will continue safety follow-up observations  
765 even after discontinuation.  
766

767 **15. Storage and Disposal of Study Records and Data (Including Retention Period)**

768 The principal investigator shall prepare and maintain records regarding:

- 769       1. Identification of each study participant.

2. Clinical care and testing performed for participants.
3. Details related to study participation.

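### Device-triggered final readings, an FAS treatment condition not defined by arm, and a device-based Day 1 can make time at risk and the analysed population differ between arms

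*Protocol*

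**What the plan says.** **Early removal.** Section 4(4)②, Comparative Period – Intervention Group, says that in the circumstances above the "device will be removed and final assessments performed". Spontaneous loss of the device is treated separately: its date and time are recorded, and no assessment is triggered. Section 14(5) states that "Participants who have received the investigational device will continue safety follow-up observations" after discontinuation, and does not mention efficacy visits. The Section 5 schedule has a discontinuation column, not limited by arm, beside the end-of-period visit (window ±7 days). The timing note in Section 6(2) lists end or discontinuation of the comparative period as alternatives, for the secondary items.

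**Endpoint.** Section 8(2) counts as success either no mucositis at the target site before and after the evaluation period, or a fall from baseline Grade 1–3.

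**Analysis set.** The FAS in Section 8(1) is defined as "All participants who were randomized, received treatment, and had at least one efficacy assessment (primary or secondary". The trial is open-label (Section 4(1)). The schedule places randomisation in the screening column, before Day 1.

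**Clock.** Section 4(4)② and schedule note g define Day 1 by device application. Note g adds: "If chemotherapy is postponed, the device should be temporarily removed, and the device application date reset in accordance with the rescheduled chemotherapy". Controls record a start date for the comparative period, and the target site is fixed on Day 1 for them too (note at the start of Section 6). No sentence resets their Day 1.

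**Sample size.** Section 7 assumes "50% in the intervention group and 25% in the control group". "With a two-sided significance level of 5% and 90% power", it concludes that "77 participants per group (total n=154) are required".

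**The concern.** Success by prevention gets easier the sooner the mouth is examined. A mucositis-free participant whose device is deliberately taken out before chemotherapy toxicity develops can be given a final reading then, and that reading satisfies the prevention definition. Controls have no device to remove in the comparative period, so nothing mirrors this route. Removal and stopping are also decided with allocation known.

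The other two provisions have the same structure. If treatment in the FAS means the device, a participant allocated to it but never fitted leaves the analysis, while controls qualify through routine care. If only the device application date is reset when chemotherapy is postponed, the reading day relative to chemotherapy can differ between arms. At stake is whether the primary test in a confirmatory trial compares the randomised groups over equal time at risk.

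**Working it through.** **1. The plan's own figure.** Inputs from Section 7: 50% v 25%, two-sided 5%, 90% power, Pearson chi-square, equal groups. With pooled rate 0.375:

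n = [1.960·√(2·0.375·0.625) + 1.2816·√(0.5·0.5 + 0.25·0.75)]² / 0.25² = (1.342 + 0.848)² / 0.0625 = 76.7, so 77 per arm.

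This reproduces the stated size. Power at 77 per arm is 90.1% by normal approximation and 90.6% by exact enumeration. The sample size calculation is not in error.

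**2. Can an early reading become the primary outcome?** The passages fit together as follows:
- The assessments at removal are called final.
- After discontinuation the text promises safety follow-up and is silent on the scheduled efficacy visit.
- The prevention definition has no minimum interval.
- No passage says that a discontinuation reading is the primary outcome, and none says that it is not.

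Following the text can therefore leave the early reading as the only one available.

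**3. Size if it does.** The protocol gives no removal rate, so this step is assumption. Take no true effect, a true rate of 25% in both arms, a fraction e of the device arm read early with success rate s, and no early readings among controls. The device-arm rate is p₁ = 0.25(1 − e) + s·e. Rejection rates come from exact enumeration of the two-sided Pearson test at 77 per arm (5.0% when p₁ = 25%).

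| e | s = 50% | s = 75% | s = 100% |
|---|---|---|---|
| 5% | p₁ 26.3%: 5.4% | 27.5%: 6.5% | 28.8%: 8.2% |
| 10% | 27.5%: 6.5% | 30.0%: 10.7% | 32.5%: 17.6% |
| 15% | 28.8%: 8.2% | 32.5%: 17.6% | 36.3%: 32.8% |

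If those read early succeed at the common 25%, nothing shifts.

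**4. FAS exclusion, if treatment means the device.** Suppose a fraction e is never fitted and would have had success rate q, again with no true effect. The analysed device arm has rate (0.25 − e·q)/(1 − e).
- e = 10%, q = 0: 0.25/0.9 = 27.8% in 69 participants, rejection 6.4%.
- e = 10%, q = 10%: 0.24/0.9 = 26.7%, rejection 5.4%.
- e = 20%, q = 0: 0.25/0.8 = 31.3% in 62 participants, rejection 12.3%.

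**5. Clock.** Suppose chemotherapy is postponed by k days. In the device arm Day 1 moves with it. A control whose Day 1 is not reset is read k days sooner relative to chemotherapy. With an assumed k of 7 and a 21-day period, that is 14 days against 21. A shorter interval makes prevention easier for the control, so this route would tend to work against the device.

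**6. Cost of the remedies.** If 10% of the device arm are never fitted, respond at 25% and are kept, the rate is 0.9·50% + 0.1·25% = 47.5%. Exact power is then about 84% (83.4% by normal approximation). If instead 10% of the device arm only are imputed as non-success, the rate is 0.9·50% = 45% and exact power falls from 90.6% to 75.2%.

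**The case against.** The best defence is that the text does not say most of what a suspicious reader might infer from it.

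- *Only the device arm is ever read early.* Not supported. The discontinuation visit and the reasons in Section 14(5) apply to both arms; only the device-triggered route is one-sided.
- *A device that falls out brings the reading forward.* Not supported. Dislodgement is only recorded.
- *Efficacy visits stop after removal.* Not stated. The text says that safety follow-up continues and leaves the rest open.
- *Never-fitted participants are dropped, and this is bound to happen.* Not supported. The intervention is standard care plus device, so such a participant may still have received treatment. The 56-day window covers all of screening and does not give the gap from randomisation to Day 1.
- *Every route favours the device.* Not so. The clock may favour controls, and early reading can count against the device where an existing lesion has had less time to improve.

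These points stand and limit the finding. One counter-argument does not stand: that controls are covered because removal and discontinuation are handled identically. That line directly follows the one on applying the device to controls in the continuous period, and in the comparative period controls have nothing to remove.

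It can also be said that premature readings belong in the analysis plan. That holds for how they are analysed. It does not hold for collection: a scheduled reading that was never taken cannot be recovered later.

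**Conclusion.** The concern holds as a gap that can produce differential time at risk, not as demonstrated bias. The early-reading route is the firmest part: it is written for one arm in the comparative period, nothing preserves the scheduled reading, and the prevention definition accepts any interval. Its likely direction favours the device for prevention. The FAS wording permits allocation-dependent exclusion on one of two readings. The Day 1 wording leaves postponed controls undefined.

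The rejection rates in the brief assume that no control is read early. The 17.6% is a worst case in which every early reading is a success. A reader might go further and quote about 33%; that needs 15% of the device arm read early with every reading a success, and the documents support neither assumption.

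**What to change.** 1. State that the end-of-period CTCAE v3.0 assessment is kept for every participant after device removal, unless consent is withdrawn, and that this in-window reading is the one used for the primary endpoint.
2. Make the primary analysis set all randomised participants as allocated. Handle missing or out-of-window readings by one rule applied alike to both arms, with non-success imputation as a sensitivity analysis. It should not be the primary rule, given the loss of power shown above if it falls mainly on the device arm.
3. Reconcile the Section 4(4)② text for both groups with schedule note g, so that Day 1, its reset on postponement and the reading day are defined the same way in both arms. The actual chemotherapy date, already recorded under note g, can serve as the common anchor.

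The cost is protocol wording and a few more retained visits; the end-of-period visit already exists. Keeping never-fitted participants dilutes the effect somewhat, and the roughly 84% power in that scenario should be weighed openly. None of this changes when a device is removed or re-applied.
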